### Follow up of women and infants

All details of delivery, maternal assessments and admittance during pregnancy are recorded in the case record form that is accessible through the website. In case of admittance of one or more children to the neonatal intensive care unit, details of this admittance are also recorded. The main outcome parameter, a composite neonatal mortality and morbidity, will be measured until 6 weeks after the expected term date of delivery.

Long-term follow up of children is desirable, but is depending on future funding

### Economic evaluation

#### General considerations

The economic evaluation will be performed from a societal perspective, with the costs per unit reduction in the primary outcome ('bad neonatal outcomes') as the primary outcome measure. The appropriate type of economic evaluation is conditional on the results. We hypothesize that when a pessary is effective, this intervention will be associated with less neonatal health care utilization, as well as less burden to parents (time costs) and absence from paid work (productivity costs). Therefore, the primary analysis will be a cost-effectiveness analysis that evaluates costs associated with an improved neonatal outcome, expecting the peccary intervention to be dominant (better health at lower costs). With a study horizon of 12 months after delivery, no discounting will be applied. Study specific costs will be excluded from the analyses.

### Cost analysis

We will differentiate between direct medical, direct non-medical and indirect costs. Within direct medical costs, the process of care is distinguished into three stages: antenatal stage, delivery/childbirth and postnatal stage. In the antenatal stage, costs are generated by health care utilization related to the placement and check of the peccary, hospital care and outpatient visits. Costs during childbirth are dominated by the course of childbirth and type of delivery. In the postnatal stage, costs are generated by hospital-based maternal care (hospitalisation etc.), neonatal care (admission to NICU/medium care or maternity ward, related diagnostic care and treatment, outpatient visits), primary care and informal care.

If neonatal health is suboptimal, further direct medical, direct non-medical and indirect costs may occur. Hence, for these infants, resource use of infants and/or parents is measured during 12 months after childbirth. Direct non-medical costs in the antenatal and postnatal stages are generated by travel to and from health care providers, and time costs as the result of household shifts. Indirect costs are associated with lost productivity due to absence from paid work, predominantly in the postnatal stage.

### Statistical issues

#### Sample size

The sample size is calculated based on the primary outcome 'bad neonatal outcome'. In the control group, 'bad neonatal outcome' is expected in 7.2% of the children (1.8%*77% + 5.4%*35% + 7.2%*12% + 35.6%*8% + 50%*.5% = 7.2%). In this calculation, the first rate represents the probability that a patient delivers at that gestational age, whereas the second rate represents the probability of 'bad neonatal outcome' at that particular gestational age. In case of treatment, 'bad neonatal outcome' is then expected in 3.9% of the children (0.9%*77% + 2.7%*35% + 3.6%*12% + 17.8%*8% + 75%*.5% = 3.9%).

Because the outcomes in children from multiple pregnancies are to a certain extent non-independent, we adjusted our sample size assuming a correlation of 0.6 for composite neonatal morbidity between two children born from the same pregnancy[11]. Using a two-sided test with an alpha of 0.05 and a power of 0.80 we need 330 women in the control group and 330 in the intervention group (total of 660 women).

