**Methods/Design:**

We aim to investigate the hypothesis that prophylactic use of a cervical pessary will be effective in the prevention of preterm delivery and the neonatal mortality and morbidity resulting from preterm delivery in multiple pregnancy. We will evaluate the costs and effects of this intervention. At study entry, cervical length will be measured. Eligible women will be randomly allocated to receive either a cervical pessary or no intervention. The cervical pessary will be placed in situ at 16 to 20 weeks, and will stay in situ up to 36 weeks gestation or until delivery, whatever comes first.

The primary outcome is composite bad neonatal condition (perinatal death or severe morbidity). Secondary outcome measures are time to delivery, preterm birth rate before 32 and 37 weeks, days of admission in neonatal intensive care unit, maternal morbidity, maternal admission days for preterm labour and costs. We need to include 660 women to indicate a reduction in bad neonatal outcome from 7.2% without to 3.9% with a cervical pessary, using a two-sided test with an alpha of 0.05 and a power of 0.80.

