### Participants

All women presenting with a multiple pregnancy between 12 and 19 weeks of gestation are eligible for the study. We propose to also include women with monochorionic pregnancies as well as women with a triplet pregnancy or women with a previous preterm birth. Women with multiple pregnancies in which at least one of the foetuses has major congenital anomalies known at study entry will not be included. Gestational age will be determined from the menstrual history and confirmed from the measurement of foetal crown-rump length (of the bigger twin) at a first-trimester scan.

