### Procedures, recruitment, randomisation and collection of baseline data

All eligible women who present at one of the participating clinics will be referred to an obstetrician or a specifically appointed research nurse/midwife for counselling. They will receive an information sheet and, where possible, are given two weeks time to reflect on participation.

Once a patient has given informed consent, and the patient data have been entered in a web-based database, randomisation will be done over the internet.

Randomisation will be stratified for centre, parity (previous vaginal delivery or not), chorionicity (multichorial versus monochorial) and number of multiples (twin or higher order gestation).

We will apply block randomisation with a variable block size and a minimalisation procedure. The pessaries will be packaged according to the randomisation sequence at the central consortium office in Amsterdam, the Netherlands. Randomisation will be 1:1 for cervical pessary versus no treatment.

The study will not be blinded.

Baseline demographic, past obstetric and medical histories will be recorded for all women. Cervical length will be measured by transvaginal ultrasound at the time of randomisation or at the next visit.

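### The stated 660 women give about 54% power, not 80%, under the protocol's own rates and within-pregnancy correlation of 0.6; about 1,208 women would be needed

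*Protocol article*

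**What the plan says.** The protocol article, Statistical issues, Sample size, sets out every input.

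- Control rate: "In the control group, 'bad neonatal outcome' is expected in 7.2% of the children".
- Pessary rate: "In case of treatment, 'bad neonatal outcome' is then expected in 3.9% of the children".
- Clustering: "we adjusted our sample size assuming a correlation of 0.6 for composite neonatal morbidity between two children born from the same pregnancy".
- Error rates: "Using a two-sided test with an alpha of 0.05 and a power of 0.80".
- Result: "we need 330 women in the control group and 330 in the intervention group (total of 660 women".

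The Abstract, Methods/Design, repeats the claim: "We need to include 660 women to indicate a reduction in bad neonatal outcome from 7.2% without to 3.9% with a cervical pessary". Allocation is equal ("Randomisation will be 1:1 for cervical pessary versus no treatment", in the section on procedures and randomisation). The Sample size section shows no formula for the step from rates to number of women. It states no allowance for dropout or anything else that would change the result.

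**The concern.** Both rates are proportions of children, while the sample size counts women. Each twin pregnancy contributes two children whose outcomes are positively correlated, so the number of women must be larger than it would be for independent children. The stated 330 per arm is smaller than even the independent-children figure. The text therefore describes an adjustment whose direction the number does not show.

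The trial is justified in the Abstract and the Discussion by the lack of adequately powered studies of a device that some gynaecologists already use. If its real power at the planned effect is little above one half, a true benefit of the planned size has a chance of about 46% of ending in a non-significant result. A reader who relies on the stated 80% would give such a result too much weight as evidence against an effect.

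**Working it through.** **Inputs** (Sample size section unless noted): p1 = 0.072, p2 = 0.039, two-sided alpha 0.05 (z = 1.96), power 0.80 (z = 0.8416), correlation 0.6, 330 women per arm, 1:1 allocation (section on procedures and randomisation). Assumption: all pregnancies are twins, so 330 women supply 660 children per arm.

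**Step 1: the rates reproduce.**
- Control: 1.386 + 1.890 + 0.864 + 2.848 + 0.250 = 7.238%, rounded to 7.2%.
- Pessary: 0.693 + 0.945 + 0.432 + 1.424 + 0.375 = 3.869%, rounded to 3.9%.

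The fault is therefore in the step from rates to sample size.

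**Step 2: independent children.** With mean rate 0.0555,

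n = [1.96·√(2·0.0555·0.9445) + 0.8416·√(0.072·0.928 + 0.039·0.961)]² / 0.033²
= (0.6346 + 0.2718)² / 0.001089 = 754.4.

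This is 755 children per arm, or 755/2 = 377.5, rounded up to 378 women. It already exceeds 330.

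**Step 3: add the stated correlation.** The design effect for pairs is 1 + (2 − 1)·0.6 = 1.6. Women per arm = 754.4·1.6/2 = 603.6, so 604 per arm and 1,208 in total.

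**Step 4: power with 330 women per arm.** The effective number of children is 660/1.6 = 412.5 per arm.

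Power = Φ[(0.033·√412.5 − 0.6346) / √(0.072·0.928 + 0.039·0.961)] = Φ[(0.6702 − 0.6346)/0.3229] = Φ(0.110) = 0.544.

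With zero correlation, √660 replaces √412.5: Φ[(0.8478 − 0.6346)/0.3229] = Φ(0.660) = 0.745. A simulation of correlated pairs analysed with a cluster-robust test agrees: 54.6% at 330 per arm and 80.1% at 604 per arm.

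**Step 5: can any reading give 330?**

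| Reading | Women per arm for 80% | Power with 330 |
|---|---|---|
| Correlation 0.6, rounded rates | 604 | 54.4% |
| Correlation 0.6, unrounded rates | 580 | 56.1% |
| Correlation 0.6, unpooled variance | 601 (601.4 before rounding) | – |
| Correlation 0.6, arcsine | 591 (591.3 before rounding) | – |
| Correlation 0.6, continuity correction | 651 (651.2 before rounding) | – |
| Woman as unit, at least one affected child | 553 | 58.1% |
| All pregnancies triplets, correlation 0.6 | – | 58.0% |
| Correlation 0.4 | 529 | 60.0% |
| Correlation 0.2 | 453 | 66.7% |
| Correlation 0 | 378 | 74.5% |

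For the woman as unit, P(at least one) = 2p − [p² + 0.6·p(1 − p)], which is 9.9% against 5.4%. For triplets, the design effect is 1 + 2·0.6 = 2.2 and the effective number is 990/2.2 = 450 children.

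Only one variant comes close to 330: a one-sided test with continuity correction and no correlation adjustment, at 327. It contradicts both the stated two-sided test and the stated adjustment. Taken backwards, 330 twin pregnancies per arm would need a design effect of 660/754.4 = 0.875, that is, a correlation of about −0.13.

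**Step 6: what 660 women can detect.** At 412.5 effective children per arm and a control rate of 7.2%, power is 80.6% for a pessary rate of 2.9%. That is a relative risk of 0.029/0.072 = 0.40, against the planned 0.039/0.072 = 0.54.

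**The case against.** The strongest reply is that 54% is more exact than the document allows.

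- **Meaning of the correlation.** The Sample size section does not define the measure and takes it from a cited source. If 0.6 were a correlation on a latent (tetrachoric) scale, the correlation of the binary outcomes would be about 0.30 at 7.2% and 0.26 at 3.9%. Power would then be about 63% to 65%, and about 475 to 490 women per arm would be needed. This stands as a reason to state the condition. The intraclass reading is the ordinary one for text about the correlation of an outcome between two children, and either reading leaves power well short of 80%.
- **Higher-order pregnancies.** The Participants section says "We propose to also include women with monochorionic pregnancies as well as women with a triplet pregnancy", with no share given. This also stands as a condition, but a weak one: even if every pregnancy were a triplet, power at correlation 0.6 would be 58.0%. The statement that 330 is too few at zero correlation needs fewer than 754.4/330 = 2.29 children per woman on average, which is very likely but is an assumption.
- **Origin of 330.** No formula is shown, so one cannot say whether the adjustment was omitted or misapplied, or whether an input was misreported. That is right. The finding is only that 330 does not follow from what is stated.
- **Interpretation of results.** Data analysis already plans relative risks with 95% confidence intervals, and the Discussion looks ahead to pooling with other trials. This softens the risk of misreading a null result but does not correct the stated power.

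Condensation into an article does not explain the gap either, because the inputs and the result are both printed and disagree.

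**Conclusion.** The concern holds. The sample size and the 80% power stated in the Sample size section and the Abstract do not follow from the protocol's own inputs. For twins, with 0.6 taken as the intraclass correlation of the binary outcome and the rounded rates, 660 women give 54.4% power, and 80% needs about 1,208 women, 1.83 times the stated number (1,208/660). Other readings move the power to between 56% and about 65% at the stated correlation, and to 74.5% at zero correlation with rounded rates (76.2% unrounded). For twin pregnancies, none of the readings tried with a two-sided test and a non-negative correlation reaches 80%. Since this concerns the primary outcome and appears in both abstract and methods, it must be corrected.

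**What to change.** In the Sample size section and in the Abstract, Methods/Design, do one of two things.

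1. **Restate the power.** For example: *Assuming twin pregnancies and an intraclass correlation of 0.6 (design effect 1.6), 330 women per arm give about 54% power at two-sided alpha 0.05 to detect 7.2% versus 3.9%, and 80% power only for a fall to about 2.9%. For 7.2% versus 3.9%, 80% power would need about 604 women per arm.*
2. **Show the calculation.** If a rate, the correlation or the sidedness was misreported, give the correct input and the formula, so that 330 can be reproduced.

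In either case, define which correlation is meant and state the assumed number of children per pregnancy.

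The cost is protocol wording only, though the stated power becomes less favourable under the first option. Whether to enlarge the trial is a separate decision for the sponsor.

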### Data analysis

Data will initially be analysed according the intention to treat method. The main outcome variable, 'bad neonatal outcome', will be assessed by calculating rates in the two groups, relative risks and 95% confidence intervals as well as numbers needed to treat. To evaluate the potential of each of the strategies, we will also perform a par protocol analysis, taking into account only those cases that were treated according to protocol.

Time to delivery will be evaluated by Kaplan-Meier estimates, with account for differing durations of gestation at entry, and will be tested with the logrank test. The other secondary outcome measures will be approached similarly to the primary outcome measure.

We plan a separate analysis of women with a cervical length below 25 mm at 18 tot 22 weeks, and we will look at interaction between cervical length and treatment effect.

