### Outcome measures

The main outcome parameter is the composite morbidity rate of children in the two groups. This composite morbidity rate contains the following variables: periventricular leukomalacia (PVL), severe Respiratory Distress Syndrome (RDS), Broncho Pulmonal Dysplasia (BPD), Intraventricular Haemorrhage II B or worse, Necrotizing Enterocolitis (NEC), proven sepsis and death before discharge from the nursery 24. They will be measured until 6 weeks after the expected term date of delivery.

Secondary outcome measures are time to delivery, preterm birth rate before 32 and 37 weeks, days of admission in neonatal intensive care unit, maternal morbidity, maternal admission days for preterm labour and costs. At present, a longer follow-up is not planned.

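### The primary analysis does not carry forward the within-pregnancy correlation of 0.6 assumed for the sample size; if children were analysed as independent, a nominal 5% test would run at about 12%

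*Protocol article*

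**What the plan says.** Women are randomised 1:1 to pessary or no treatment (Procedures, recruitment, randomisation and collection of baseline data). The primary outcome is counted in children: "The main outcome parameter is the composite morbidity rate of children in the two groups" (Outcome measures). The planning rates in Sample size are also per child, 7.2% against 3.9%.

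Sample size recognises the dependence between siblings: "Because the outcomes in children from multiple pregnancies are to a certain extent non-independent", the number of women is said to have been adjusted using a correlation of 0.6.

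Data analysis then says that the primary outcome "will be assessed by calculating rates in the two groups, relative risks and 95% confidence intervals as well as numbers needed to treat". It names no clustered model, robust variance or pregnancy-level unit. It also does not say that siblings are taken as independent. Time to delivery has its own method (Kaplan-Meier and logrank). For the rest: "The other secondary outcome measures will be approached similarly to the primary outcome measure". By Outcome measures, the rest includes days in neonatal intensive care and maternal admission days for preterm labour.

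**The concern.** When women are randomised and children are counted, two siblings carry less information than two unrelated children. The sample-size section accepts this, but the analysis section describes a two-group comparison of child rates and does not mention it. A reader who follows the analysis section literally could enter the children into a standard two-by-two table. The interval for the primary outcome would then be too narrow and the p-value too small, so the trial could claim a benefit or a harm that its data do not support.

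Two smaller points follow from the same text. The number needed to treat has no stated unit, although the pessary is given to a woman and the outcome is counted in her children. And relative risks and numbers needed to treat, carried over to the other secondary outcomes, do not fit outcomes measured in days.

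**Working it through.** **Inputs.** From Sample size: two-sided alpha 0.05, power 0.80, 7.2% and 3.9% of children, correlation 0.6, 330 women per arm. From Participants: twins, with triplets allowed. Assumption for the arithmetic: all pregnancies are twins, so there are 660 children per arm.

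**The plan's own figures.**
- Rates: the published sums give 7.238% and 3.869%, which agree with 7.2% and 3.9%.
- Sample size: the usual two-sided formula for two proportions gives 755 children per arm. With the design effect 1 + (2 − 1) × 0.6 = 1.6, that is 755 × 1.6 / 2 = 604 women per arm. Without any correlation it is 755 / 2 ≈ 378. The stated 330 is not reproduced. That is a separate matter; here it means only that the adjustment described in Sample size gives no assurance that the correlation is handled elsewhere.

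**Size of an unadjusted test.** The standard error is too small by √1.6 = 1.265. The true two-sided size is 2 × (1 − Φ(1.96 / √(1 + ρ))):

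| Correlation ρ | True size | Coverage of a nominal 95% interval |
|---|---|---|
| 0.3 | 8.6% | 91.4% |
| 0.5 | 11.0% | 89.0% |
| 0.6 | 12.1% | 87.9% |
| 0.7 | 13.3% | 86.7% |

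A simulation of 330 twin pairs per arm at ρ = 0.6 (200,000 runs, no treatment effect) agrees:

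| Common rate | Pooled z test | Standard log relative-risk interval | Cluster-robust variance |
|---|---|---|---|
| 5.55% | 12.2% | 11.7% | 5.0% |
| 7.2% | 12.1% | 11.8% | 5.0% |

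Triplets would raise the figure slightly, since their design effect is 1 + 2 × 0.6 = 2.2.

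**Interval at the planned rates.** Relative risk = 0.039 / 0.072 = 0.54, with log −0.613.
- Unadjusted standard error of the log: √(0.928 / (660 × 0.072) + 0.961 / (660 × 0.039)) = √(0.0195 + 0.0373) = 0.238. Interval exp(−0.613 ± 1.96 × 0.238) = 0.34 to 0.86; p = 0.010.
- With clustering: 0.238 × 1.265 = 0.302. Interval exp(−0.613 ± 1.96 × 0.302) = 0.30 to 0.98; p = 0.042.

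With these standard errors held fixed, the unadjusted analysis reaches significance at a relative risk of exp(−0.467) ≈ 0.63 or lower, and the clustered one at exp(−0.591) ≈ 0.55 or lower. Results between these two values are where the choice would change the conclusion.

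**Number needed to treat at the planned rates.**
- In children: 1 / 0.033 ≈ 30.
- In women, per bad outcome averted: 1 / (2 × 0.033) ≈ 15.
- In women, to spare one woman any affected child: the probability of at least one affected twin is 2p − [p² + 0.6p(1 − p)], which is 9.87% and 5.40%; 1 / 0.0447 ≈ 22.

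One set of rates thus gives 30, 22 or 15, depending on a unit that the article does not state.

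**The case against.** The strongest reply is that the article states no error. It lists effect measures and leaves the variance method open. A relative risk with a 95% interval is also exactly what a clustered model would report. The article condenses a fuller protocol, and a statistical analysis plan may exist; a model for correlated children is typical content for either. The authors plainly knew of the dependence, since they cite it for the sample size.

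Much of this stands. A reader might infer that the planned intervals are ordinary ones and that this trial's false-positive rate is 12%. The article supports neither statement: the 12% holds only for an unadjusted analysis, all-twin pregnancies and a correlation of 0.6. At exactly the planned rates both analyses are significant at 5%, so the conclusion there would not change.

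It does not dispose of the point. The unit of analysis is basic to a primary comparison in which women are randomised and children counted. The same section finds room for other refinements: differing gestation at entry for time to delivery, and an interaction with cervical length. The correlation is treated as important enough to drive the design and is then absent from the analysis that should match it.

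A reader might also infer that the problem runs through all secondary outcomes and costs. It does not. Preterm birth rates, maternal morbidity and maternal admission days are per-woman outcomes, and costs have their own evaluation under Economic evaluation and Cost analysis. The unit of the number needed to treat is a reporting choice; it only has to be stated. What remains among the secondary outcomes is the poor fit of the carried-over approach to the two outcomes measured in days, and clustering for NICU days if these are counted per child.

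**Conclusion.** The concern holds in conditional form. The protocol article assumes a within-pregnancy correlation of 0.6 for its sample size and does not carry it into the stated analysis of a child-level primary outcome. If children were analysed as independent, the true two-sided size would be about 12% at correlation 0.6, with coverage of about 88%. A correlation of 0.3 to 0.7 gives a size of about 9% to 13%. These figures assume twins throughout and take the planning correlation at face value.

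The text does not show that the trial will be analysed this way, so the finding is a gap that affects inference on the primary outcome and should be closed, not proof of a wrong analysis. Separately, the instruction to treat the other secondary outcomes like the primary one does not suit NICU days or maternal admission days, whatever a fuller plan adds on clustering.

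**What to change.** In Data analysis:
- State that child-level outcomes are analysed with allowance for clustering by mother, for example with a log-binomial or modified Poisson GEE with robust variance, or that they are analysed at pregnancy level.
- State whether the number needed to treat counts women or children.
- For NICU days and maternal admission days, replace the carried-over approach with a difference in days and a suitable interval, clustered by mother for NICU days.

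This costs a few lines of text and needs no new data. The downside is wider intervals for child-level outcomes, by a factor of about 1.26 on the log scale at correlation 0.6. With 330 women per arm and the planned rates, a clustered analysis has about 54% power. That shortfall comes from the number of women, not from the clustered method, and an unadjusted analysis would not be a legitimate way to avoid it.

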## Methods/Design

### Aims

We will use a randomised trial (the ProTwin-trial: Pessaries in multiple pregnancy as a prevention of preterm birth: the ProTwin Trial) to assess the effect of a cervical pessary on neonatal outcome.

The study is set in the Dutch Obstetric Research Consortium, a collaboration of obstetric practices in the Netherlands. Approximately 50 clinics, including academic hospitals, non-academic teaching hospitals and non-teaching hospitals will participate in this trial.

To conduct this trial we got approval from the Medical Ethics Committee, Academic Medical Centre, Amsterdam, The Netherlands (MEC O9/1O7).

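### Randomisation is stratified on four factors, but the primary analysis as described does not use them; adjusting for them is a small, inexpensive improvement

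*Protocol article*

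**What the plan says.** On allocation, the section on procedures, recruitment and randomisation states: "Randomisation will be stratified for centre, parity (previous vaginal delivery or not), chorionicity (multichorial versus monochorial) and number of multiples" (twin or higher order). It continues: "We will apply block randomisation with a variable block size and a minimalisation procedure", and "Randomisation will be 1:1 for cervical pessary versus no treatment". The Aims section gives the scale: "Approximately 50 clinics, including academic hospitals, non-academic teaching hospitals and non-teaching hospitals will participate in this trial".

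On analysis, the Data analysis section describes the assessment of the main outcome as "calculating rates in the two groups, relative risks and 95% confidence intervals", together with numbers needed to treat, under intention to treat. It says that the remaining secondary outcomes, apart from time to delivery, are handled in a similar way. The stratification factors are not mentioned there. For time to delivery, the same section does state an allowance, for gestational age at entry. It also plans an analysis of the interaction between treatment and cervical length.

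The Sample size section works per child: "In the control group, 'bad neonatal outcome' is expected in 7.2% of the children", against 3.9% with a pessary. It assumes a correlation of 0.6 between children of one pregnancy and 330 women per arm.

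**The concern.** Stratified or minimised allocation makes the arms more alike on the chosen factors than simple randomisation would. If those factors predict outcome, the true sampling variance of the treatment comparison falls. A standard two-group variance does not reflect this, because it still counts the between-stratum variation as noise. The resulting interval is on average too wide and the test rejects a little less often than its nominal level. Any imbalance that remains in a prognostic factor also stays in the crude estimate, whereas adjustment removes it. At stake are a little precision and the chance to settle the choice between a crude and an adjusted estimate before results are known in an unblinded trial.

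**Working it through.** **Inputs from the protocol article.** Rates 7.2% and 3.9% per child; correlation 0.6; 330 women per arm; two-sided alpha 0.05; about 50 clinics. I take two children per woman.

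**The plan's own rates.** Control: 1.386 + 1.890 + 0.864 + 2.848 + 0.250 = 7.238%. Pessary: 0.693 + 0.945 + 0.432 + 1.424 + 0.375 = 3.869%. Both agree with the stated figures after rounding.

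**Baseline power without adjustment.**
- Effective children per arm: 660 / (1 + 0.6) = 412.5.
- SE under the null: sqrt(2 × 0.0555 × 0.9445 / 412.5) = 0.01594.
- SE under the alternative: sqrt((0.072 × 0.928 + 0.039 × 0.961) / 412.5) = 0.01590.
- Power: Φ((0.033 − 1.96 × 0.01594) / 0.01590) = Φ(0.110) = 0.544.

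This is well below the stated 0.80. That shortfall is a separate sample-size matter; 0.544 serves here only as the starting value.

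**How much the factors might explain (assumed).** For a binary factor with prevalence q and relative risk r, at mean risk 0.0555, the lower-risk level has b = 0.0555 / (1 − q + qr). The variance explained is q(1 − q)[b(r − 1)]². The variance of a woman's mean outcome is 0.0555 × 0.9445 × 1.6 / 2 = 0.0419.
- Monochorionic, q = 0.20, r = 2: 0.000342 / 0.0419 = 0.8%.
- No previous vaginal delivery, q = 0.55, r = 1.5: 0.000117 / 0.0419 = 0.3%.
- Triplet, q = 0.03, r = 3: 0.000319 / 0.0419 = 0.8%.

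The sum is about 1.9%, treating the factors as independent. I use 1–3% as the working range.

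**Effect of adjustment.** With a share R² explained, the SE is multiplied by sqrt(1 − R²). The last column assumes full balance on the factors.

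| R² | crude interval wider by | power, adjusted | type I error, crude test |
|---|---|---|---|
| 1% | 0.5% | 0.548 | 0.049 |
| 2% | 1.0% | 0.552 | 0.048 |
| 3% | 1.5% | 0.557 | 0.047 |

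A wider range of 0.5% to 5% gives power from 0.546 to 0.565.

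**Simulation check.** 660 twin pregnancies, 20% monochorionic, half parous, arms balanced within these strata, clustering handled in both analyses, 4000 runs. With relative risks 2 and 0.67, the adjusted SE was 0.6% smaller and power went from 0.544 to 0.547. With 3 and 0.5, the SE was 1.8% smaller and power went from 0.560 to 0.572.

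**Residual imbalance.** The strata form 50 × 2 × 2 × 2 = 400 cells for 660 women, or 1.65 per cell. Simulating stratified permuted blocks alone leaves a between-arm difference with SD 7.2 to 8.4 among about 132 monochorionic women, against sqrt(132) = 11.5 under simple randomisation. With control risks of about 6% and 12%, a difference of 8 women shifts the arm contrast by 8/330 × 6 = 0.15 percentage points, less than a tenth of the 1.6-point SE.

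**Room for covariates.** Expected affected children: 660 × 0.072 + 660 × 0.039 = 73. That is about 1.5 per centre.

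**The case against.** The strongest objection is that the article never calls the analysis unadjusted. A relative risk with an interval can come from a model, and a condensed article often leaves covariates to a full protocol or SAP that is not shown here. A reader might infer that the investigators decided to ignore the stratification factors; the text does not support that. What remains is that the section does describe the primary analysis, states an allowance where it intends one for time to delivery, and attaches none to the primary outcome.

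Second, the gain is slight and the error is in the safe direction. This is correct and sets the weight of the point.

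Third, protection against imbalance and the gain in precision are largely the same thing, so the two should not be added. The imbalance simulation also leaves out the minimisation that the protocol names, and so probably overstates what remains. Both criticisms stand.

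Fourth, adjustment has a cost. With about 1.5 affected children per centre, centre effects are fragile and a relative-risk model may not converge. This stands for centre. It has little force for three binary factors against 73 expected events, although the triplet term will be thinly informed.

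**Conclusion.** The point holds as a minor one. Using the factors already built into the allocation is better than the two-group comparison described. Under assumed effects explaining about 1–3% of the variance, the benefit is about 0.5–1.5% of interval width and about one power point. The prevalences and relative risks behind that range are assumptions; the article gives none.

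Three stronger conclusions are tempting and are not supported. The crude estimate is not biased, and leaving the factors out does not raise the type I error. That statement presumes a variance that allows for clustering within mother, for which the Data analysis section names no method; this is a separate and larger question. The omission is not a pure loss either, because a simple comparison avoids sparse-data problems. Finally, the low power at 660 women does not make this point weightier, since one power point does not repair it.

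**What to change.** Add a sentence to the Data analysis section: the primary relative risk will be estimated from a model that allows for clustering of children within mother and is adjusted for parity, chorionicity and number of fetuses. State how centre is handled: a random effect or hospital type, omitted if the model does not converge, and not fixed effects for some 50 clinics. Report the crude rates, crude relative risk and number needed to treat beside it. If a full protocol or SAP already says this, a reference to it is enough.

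The cost is a sentence or two of text and a slightly more complex model in which the triplet term rests on few pregnancies. No new data are needed, because all the factors are known at randomisation.
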